## Research question

2

Is a culturally adapted cardiovascular dance program (Fitfolk) as effective as, or more effective than, a conventional physical exercise program in improving physical health, health-related quality of life, and exercise motivation, and in reducing perceived barriers to physical activity among rural Indigenous women with overweight or obesity and cardiometabolic risk in the commune of Padre Las Casas, Chile?

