Cardiovascular dance modalities -i.e., dance-based, music-driven aerobic exercise- such as Zumba have demonstrated high adherence and beneficial effects on weight maintenance and cardiorespiratory fitness (21). “Fitfolk,” a culturally grounded CD discipline originating in northern Chile, integrates fitness exercises with Chilean and Latin American folk music and dance, aiming to promote physical and psycho-emotional well-being while strengthening cultural identity (22). However, no studies in Chile or Latin America have evaluated Fitfolk or similar culturally adapted CD interventions as strategies to address overweight, obesity, or cardiometabolic disease, particularly among Indigenous women. To date, no randomized controlled trials have examined such interventions in rural Mapuche communities.

The comparator for this trial will be a conventional physical exercise program, defined according to current clinical guidelines and standard care practices (23, 24), and aligned with recommendations from the European Association for the Study of Obesity (25). Both intervention and control groups will receive supervised exercise three times per week for 60 min over 12 weeks, ensuring equivalent exercise dose and professional contact time, thereby allowing isolation of the cultural component as the primary differentiating factor.

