### Sample size

4.3

The sample size was determined *a priori* using G*Power software (version 3.1.9.7, Heinrich Heine University Düsseldorf, Düsseldorf, Germany) for a pre–post intervention comparison of mean differences. Based on an anticipated effect size of 0.8 for aerobic capacity, derived from previously published data (29), a minimum of 16 participants (eight per group) was required to achieve a statistical power of 80% (1 − *β* = 0.80) with a two-sided significance level of *α* = 0.05. To account for potential attrition, an additional six participants will be recruited, resulting in a total sample of 22 individuals (11 per group; Figure 1).

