### Statistical analysis

4.16

Multiple imputation methods will be employed to address missing data in accordance with the intention-to-treat principle (86). Descriptive statistics for continuous variables will be presented using measures of central tendency and dispersion, whereas categorical variables will be represented through frequencies and percentages. The Shapiro–Wilk test assesses data distribution, whereas Levene’s test evaluates the homogeneity of variances.

Non-parametric sensitivity analyses will be conducted when the criteria for normality or homoscedasticity are not met, due to the limited sample size (*n* = 22) and potential violations of parametric assumptions. Wilcoxon signed-rank tests will be used for within-group comparisons, while Mann–Whitney U tests will be applied for between-group comparisons.

A two-way repeated-measures analysis of variance (ANOVA) will be conducted to assess intervention effects, incorporating group (experimental vs. control), time (pre-intervention vs. post-intervention), and the group × time interaction as model factors. Bonferroni-adjusted *post hoc* tests will be utilized where necessary to determine statistically significant differences. Effect sizes will be computed utilizing Cohen’s d and classified as inconsequential (<0.20), small (0.20–0.49), moderate (0.50–0.79), or large (≥0.80) (87). Statistical analyses will be performed utilizing SPSS software (version 25; IBM Corp., Chicago, IL, USA), with a significance threshold established at *p* < 0.05. Graphical analyses will be conducted with GraphPad Prism (version 8, GraphPad Software, San Diego, CA, USA).

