Notably, even without statistically significant metabolic effects, the results of this study would offer important insights into the function and constraints of cultural elements in exercise-based therapies. These results may suggest that metabolic outcomes are more significantly affected by training volume and intensity than by cultural adaptation alone, or that extended intervention durations and greater community engagement are necessary to produce substantial physiological changes.

This protocol is characterized by its incorporation of stringent quantitative methods within an intercultural framework, targeting a population that has been traditionally marginalized in clinical research. The study enhances the acknowledgment of Indigenous views in health research by including Mapuche women and appreciating traditional knowledge in the intervention design. The findings may guide the formulation of intercultural health policies and community-based initiatives that integrate Indigenous identity as a fundamental element of preventive and treatment approaches.

Expected limitations encompass difficulties in maintaining long-term compliance, potential selection bias, and logistical obstacles associated with doing research in rural community environments. The study aims to produce evidence that endorses the creation of culturally customized intervention models for obesity management and enhances the cultural significance of physical and mental health promotion programs within Indigenous groups.

This protocol presents a novel, comprehensive, and culturally attuned method for addressing obesity in Mapuche women. This approach integrates scientific evidence with sociocultural context to produce transferable and socially relevant knowledge consistent with intercultural health principles, while offering a solid clinical framework to inform future interventions in Indigenous communities.

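### The research question admits equal effectiveness as an answer, but the sizing and the analysis contain only difference tests and no margin, so no planned analysis can support that answer

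*Protocol article*

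**What the plan says.** Section 2 asks whether the dance programme is "as effective as, or more effective than, a conventional physical exercise program", across physical health, quality of life, motivation and barriers. Two answers are thus admitted as favourable: equal and better.

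The comparator is an active programme. The Introduction describes the arms as matched, "ensuring equivalent exercise dose and professional contact time, thereby allowing isolation of the cultural component as the primary differentiating factor".

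Section 4.3 sizes the trial for a "pre–post intervention comparison of mean differences", with an "anticipated effect size of 0.8 for aerobic capacity, derived from previously published data". It reports that "a minimum of 16 participants (eight per group) was required to achieve a statistical power of 80" per cent, at a "two-sided significance level of *α* = 0.05". Six more women are added for attrition, giving 22 (11 per arm).

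Section 4.16 plans a repeated-measures ANOVA with group, time and their interaction, Bonferroni-adjusted post hoc tests, and a threshold of p<0.05. If assumptions fail, there are non-parametric sensitivity analyses: "Wilcoxon signed-rank tests will be used for within-group comparisons", and Mann–Whitney tests compare the arms. Cohen's d of 0.80 or more is classed as large. Section 4.12 makes intention-to-treat primary, with a per-protocol sensitivity analysis that is not tied to any non-inferiority aim.

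Section 5 considers what metabolic results without statistical significance might mean. One suggestion is that "metabolic outcomes are more significantly affected by training volume and intensity than by cultural adaptation alone". The other is that longer programmes and more community engagement are needed.

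**The concern.** A claim that one programme is as effective as another needs a stated margin and a confidence limit to compare with it. A test of no difference cannot supply this: failing to reject the null is what a small trial does most of the time, whatever the truth. Every test in section 4.16 is a difference test, and section 4.3 contains no margin. One half of the stated question therefore has no valid analysis.

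The only results that could seem to answer it are p>0.05 between arms, or improvement in both arms. The second is no better than the first. Both arms exercise and there is no untreated arm, so pre–post change mixes the programme effect with time, season and learning of the step test. At stake is a favourable conclusion about Fit-Folk drawn from an uninformative result.

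The Discussion remark is a related, smaller matter. The arms have the same session frequency, duration and contact time, so a null between-arm result says nothing about whether volume or intensity matters more than cultural adaptation.

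**Working it through.** **Inputs.** From section 4.3: effect size 0.8, two-sided α 0.05, 80% power, 16 women minimum, 22 recruited (11 per arm). From section 4.16: d ≥ 0.80 is large. Assumed here, because the article gives no figure: the non-inferiority margins, a true difference of 0 where stated, and the pre–post correlation ρ. Differences are in SDs of the change score unless noted.

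**1. The plan's own figure of 16.** Two calculations come to it or close to it, and both are difference tests.
- Paired t-test in a single group, standardised change 0.8: n = 15. For a signed-rank test with efficiency 0.955, 15/0.955 = 15.7, so 16.
- Group × time interaction with f = 0.4 and assumed ρ = 0.5: λ = f²·N·m/(1−ρ) = 0.16 × 16 × 2/0.5 = 10.24, power 84.5% (78.5% at N = 14). With 8 per arm λ = d²·n/2 = 4d², so d = √(10.24/4) = 1.6 SD between arms.

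A two-sample comparison at d = 0.8 does not give 16. It needs 26 per arm, and power is 32% with 8 per arm and 43% with 11. No version involves a margin.

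**2. Precision.** Expected 95% half-width = t(0.975, 2n−2) × √(2/n).
- 11 per arm: 2.086 × 0.426 = 0.89 SD.
- 8 per arm: 2.145 × 0.5 = 1.07 SD.

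Since 0.89 exceeds 0.80, an interval of this width around zero contains both −0.80 and +0.80. To exclude Fit-Folk being worse by 0.80, the estimate would have to favour Fit-Folk by more than 0.09 SD (0.89 − 0.80).

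**3. How often a real deficit gives p>0.05.** One minus the power of the two-sample t-test, noncentrality d·√(n/2):

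| True deficit | 11 per arm | 8 per arm |
|---|---|---|
| 0.5 SD | 80% | 85% |
| 0.8 SD | 57% | 68% |

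**4. If equal effectiveness were tested formally.** Non-inferiority, one-sided α 0.025, true difference 0. The required n per arm is for 80% power by the normal approximation.

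| Assumed margin | Needed per arm (total) | Power, 11 per arm | Power, 8 per arm |
|---|---|---|---|
| 0.3 SD | 175 (350) | 9.9% | 8.1% |
| 0.5 SD | 63 (126) | 20% | 15% |
| 0.8 SD | 25 (50) | 43% | 32% |

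Two-sided equivalence is harder. By simulation with 11 per arm, the 90% interval falls inside ±0.5 SD in about 0.1% of trials and inside ±0.8 SD in about 17%. Section 4.2 puts the whole community at about 170 members.

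**5. Sensitivity to units.** SD of change = outcome SD × √(2(1−ρ)); the two are equal at ρ = 0.5. At ρ = 0.8 the factor is √0.4 = 0.632 and the half-width is 0.89 × 0.632 = 0.56 outcome SD. It drops below 0.80 outcome SD when 2(1−ρ) < (0.80/0.89)² = 0.81, that is, when ρ exceeds about 0.6.

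**The case against.** The strongest reply is that nobody has proposed to claim equivalence. A reader might infer from section 2 that p>0.05 will be reported as equal effectiveness. The article does not support that: section 4.16 sets a threshold for significance and attaches no conclusion to missing it. The equality wording occurs in a one-sentence question. The abstract and section 3 speak of a comparison, and the anticipated results are framed as superiority on psychosocial outcomes and adherence. All this stands. The defect is what the question permits, not an announced misreading.

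A reader might also infer that the programmes will be compared through within-group tests. That is not supported either. The Wilcoxon tests are conditional sensitivity analyses, they sit beside Mann–Whitney tests, and the main model includes group × time. Reporting within-group p-values is a matter of preference and is not itself an error.

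The Discussion remark concerns secondary metabolic outcomes, is hedged, offers a second explanation and claims no equivalence. It is not evidence that equivalence will be claimed. It does give a null result a substantive reading that the design cannot support.

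Finally, section 4.1 says that a full analysis plan is public, and it is not shown here. Reporting of intervals and interpretation rules may be there, so their absence from the article is not held against it. The margin is different. It would have to drive the sample size, and section 4.3 gives a sample size without one.

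**Conclusion.** The point holds in this form: section 2 admits an answer that sections 4.3 and 4.16 cannot deliver. The conflict is inside the article and does not depend on the unseen analysis plan.

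With 11 per arm, a non-significant result is the likely outcome even when Fit-Folk is materially worse: about 80% of trials at a true deficit of 0.5 SD and 57% at 0.8 SD. These figures assume normal data, a two-sample comparison of change scores and no losses; losses make them worse. They are in SDs of change, and a pre–post correlation above about 0.6 would narrow the interval below 0.80 when expressed in outcome SDs. The non-inferiority powers rest on margins assumed for illustration. In particular, 0.8 appears in the article as an anticipated effect and as a label for a large one, never as a margin.

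**What to change.** - **Section 2:** ask for the difference between the two programmes and remove the equality half of the question.
- **Section 4.16:** state that p>0.05 is not evidence of equal effectiveness. Base conclusions on the between-group difference in change with its 95% confidence interval, and treat within-group changes as descriptive.
- **Section 5:** say that a non-significant metabolic result is inconclusive and does not show that volume and intensity matter more than cultural adaptation, because session frequency, duration and contact time are equal by design.
- **If the equality claim is kept:** fix and justify a margin on the step-test outcome before unblinding, compare the confidence limit with it, and state the low power (about 20% for an assumed 0.5 SD margin and 43% for an assumed 0.8 SD margin, under true equality).

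The first three changes are wording and need no extra participants or data. The price is that the claim of equal effectiveness will most likely not be available.

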## Study objective

3

To describe the methodological design of a randomized controlled trial aimed at evaluating the effects of a culturally adapted cardiovascular dance program (Fitfolk), compared with a conventional physical exercise program, on physical health outcomes, health-related quality of life, exercise motivation, and perceived barriers to physical activity in rural Indigenous women with overweight or obesity as key determinants cardiometabolic diseases from the commune of Padre Las Casas, Chile.

## Methods

4

### Design

4.1

This research will be structured as a randomized controlled trial (RCT) featuring two parallel arms, with blinding implemented for both the outcome assessor and the statistical analyst. The trial followed CONSORT guidelines (26) and complied with the updated SPIRIT guidelines (27) for RCTs, with the SPIRIT checklist (Supplementary Table 1). The TIDieR checklist was utilized to facilitate clear and reproducible reporting of the clinical intervention (28).

The Scientific Ethics Committee of Universidad Santo Tomás conducted a review and granted approval for the study protocol, in compliance with the ethical requirements for clinical studies (Approval code No. 231366443/2023). The RCT protocol was prospectively registered in December 2024 in the ClinicalTrials.gov database (Registration Number NCT06903455), and the comprehensive statistical analysis plan is available to the public.

### Study setting

4.2

A formal agreement was established with the Huichacura-Cayuqueo Indigenous Community of Padre Las Casas to implement the FONDEPORTE project (Project N° 2,400,120,062). This Mapuche community comprises approximately 85 families, totaling around 170 members, and is recognized as one of the largest Indigenous communities in the rural sector of the La Araucanía Region. The community’s daily practices reflect traditional Mapuche cultural patterns, which are evident in their belief systems, customary dietary practices, and habitual physical activities.

Within the context of the study, women from the community who met the predefined eligibility criteria will be identified and invited to participate through informational meetings and digital outreach strategies.

### Sample size

4.3

The sample size was determined *a priori* using G*Power software (version 3.1.9.7, Heinrich Heine University Düsseldorf, Düsseldorf, Germany) for a pre–post intervention comparison of mean differences. Based on an anticipated effect size of 0.8 for aerobic capacity, derived from previously published data (29), a minimum of 16 participants (eight per group) was required to achieve a statistical power of 80% (1 − *β* = 0.80) with a two-sided significance level of *α* = 0.05. To account for potential attrition, an additional six participants will be recruited, resulting in a total sample of 22 individuals (11 per group; Figure 1).

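### The 80% power in section 4.3 is that of a pooled pre-post test; for a between-arm difference of 0.8 SD of change, power is about 32% with 8 per arm and 43% with 11 per arm

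*Protocol article*

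**What the plan says.** Section 4.3 (Sample size) reports a G*Power calculation "for a pre–post intervention comparison of mean differences". Its inputs are an "anticipated effect size of 0.8 for aerobic capacity", 80% power and a "two-sided significance level of *α* = 0.05". It concludes that "a minimum of 16 participants (eight per group) was required to achieve a statistical power of 80" per cent. For attrition, "an additional six participants will be recruited, resulting in a total sample of 22 individuals (11 per group"). It does not say which SD scales the 0.8, and it gives no pre-post correlation.

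Elsewhere the question is a comparison between arms. Section 2 asks whether Fitfolk matches or outperforms conventional exercise. Section 4.1 specifies a randomised trial with two parallel arms. In section 4.16, a "two-way repeated-measures analysis of variance (ANOVA) will be conducted to assess intervention effects", with group, time and their interaction as factors; Mann–Whitney U is the non-parametric between-group test. The primary outcome is cardiorespiratory fitness (section 4.14.1).

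**The concern.** A pre-post calculation answers whether participants change over 12 weeks. Randomisation is there to answer whether the two programmes differ in the change they produce, and section 4.3 gives no power for that. Because the figure is quoted with a size per group, a reader will take the 80% as the power of the randomised comparison.

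Two features raise the stakes:

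- **Both arms exercise under supervision at a matched dose (section 1).** An effect of 0.8 taken from a pre-post change would plausibly overstate the difference between two active programmes. The documents give no figure for how much.
- **The research question allows for the programmes being equally effective.** A non-significant interaction in a trial described as having 80% power could be read as evidence of similarity. At the power the trial may really have, that inference would be unsafe.

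**Working it through.** **Inputs.** Effect 0.8, two-sided alpha 0.05, power 80%, 16 in total (8 per arm), raised to 22 (11 per arm), all from section 4.3. Two parallel arms come from section 4.1 and the group × time model from section 4.16. The pre-post correlation r is not stated, so values of r below are assumptions. Power uses the noncentral t or F distribution.

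**Step 1: reproduce the 16.** Paired t test on n participants, ignoring arm: noncentrality = 0.8 × √n, with n − 1 degrees of freedom.

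| Pairs | Noncentrality | Power |
|---|---|---|
| 8 | 2.26 | 49.6% |
| 14 | 2.99 | 79.0% |
| 15 | 3.10 | 82.1% |
| 16 | 3.20 | 84.8% |

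The minimum is 15, or 16 when made even for two groups. This matches the stated total, but only with both arms pooled. A paired test within one arm of 8 has 49.6% power.

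**Step 2: another route to 16.** A repeated-measures interaction calculation has noncentrality f² × N × 2 / (1 − r). With f = 0.4, r = 0.5 and N = 16 this is 0.16 × 32 / 0.5 = 10.24, and power is 84.5% (N = 14 gives 78.5%). A two-sample t test with 8 per arm has squared noncentrality d² × 8/2; setting 4d² = 10.24 gives d = 1.6. This route therefore assumes a between-arm difference in change of 1.6 SD, twice the stated 0.8. A difference of 0.8 corresponds to f = 0.2, for which N = 16 gives 32.0%.

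**Step 3: the comparison the trial makes.** With two time points, the group × time F test is equivalent to a two-sample t test on change scores: noncentrality = d × √(n/2), with 2n − 2 degrees of freedom. For d = 0.8 in SD-of-change units:

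| Per arm | Noncentrality | Power |
|---|---|---|
| 8 | 1.60 | 32.0% |
| 11 | 1.88 | 43.1% |
| 26 | 2.88 | 80.7% |

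Simulation gave 31.8% and 43.1% for 8 and 11 per arm. The smallest size reaching 80% is 26 per arm, or 52 in total, before dropout. A one-sided test would still need 21 per arm.

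**Step 4: if 0.8 is in raw-score SD units.** The SD of change is √(2(1 − r)) raw SDs, so d = 0.8 / √(2(1 − r)).

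| Assumed r | d for change | 8 per arm | 11 per arm |
|---|---|---|---|
| 0.3 | 0.68 | 24% | 33% |
| 0.5 | 0.80 | 32% | 43% |
| 0.7 | 1.03 | 49% | 64% |
| 0.8 | 1.26 | 65% | 81% |

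Power reaches 80% at r of about 0.86 with 8 per arm, and at about 0.80 with 11 per arm and no losses.

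**Step 5: detectable difference.** Solving step 3 for 80% power gives 1.51 SD of change with 8 per arm and 1.26 SD with 11 per arm.

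**The case against.** The strongest reply is that section 4.3 names a pre-post comparison and its sum is right for that test; it never says in terms that 80% applies to the between-arm contrast. That is fair as a description of the error: it is a mismatch of test, not a slip in calculation. It does not rescue the sample size, because no other justification is offered and the test named is not the one that answers the research question.

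Second, 32% and 43% are conditional on the scale of 0.8. In raw-score SD units with a high correlation, power could be adequate: 81% with 11 per arm at r = 0.8, and 91% with 8 per arm at r = 0.9. This stands, and the range must accompany the headline figures. But the documents neither state nor support such a correlation, and the 11-per-arm figures assume that none of the six allowed losses (6/22 = 27%) occurs.

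Third, the source of the 0.8 and the full analysis plan are not shown. They might explain the inputs, and the f = 0.4 route is only a conjecture about them. The published power statement is nevertheless complete in itself (software, effect, alpha, power and size) and can be judged as it stands.

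Finally, calling the trial a pilot is a matter of preference, and the abstract makes no power claim that needs correcting. Both points are accepted; neither affects the correction to section 4.3.

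**Conclusion.** The concern holds; the power statement must be corrected. The stated 16 corresponds to a pooled pre-post test, while the trial's question is the difference between randomised arms. If 0.8 is a between-arm difference in SD-of-change units (the same as raw SD units when r = 0.5), power is about 32% with 8 per arm and 43% if all 22 complete. On the raw-SD reading with r between 0.3 and 0.8, the ranges are 24–65% and 33–81%. The stated minimum of 8 per arm reaches 80% only if r is about 0.86 or higher. If 0.8 is a pre-post effect, as the wording suggests, no between-arm effect has been specified at all, and power against an active comparator would plausibly be lower still.

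**What to change.** Keep 22 participants and rewrite the power sentence in section 4.3 to:

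- name the between-arm test of change (the group × time interaction) as the one to which power refers;
- say on which scale 0.8 is measured and, if in raw-score SDs, the pre-post correlation assumed;
- report about 43% power for a between-arm difference of 0.8 SD of change if all 22 complete and about 32% if 16 do, with 80% power only for about 1.26 and 1.51 SD respectively;
- state that the primary result is the between-arm difference with its 95% CI, and that a non-significant interaction will not be taken as evidence of equal effect.

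Describing the trial as a pilot or estimation study would suit these figures but is optional; only that label would touch the abstract. The cost is a few sentences and a less favourable stated power, with no extra participants. Keeping the 80% claim at 0.8 SD of change would instead need 52 completing women, which may be out of reach in a community of around 170 members (section 4.2).
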